The pregnancy and neonatal outcomes of COVID-19 (PAN-COVID) registry will focus on miscarriage, FGR, stillbirth, preterm delivery and vertical transmission (suspected or confirmed) and early onset neonatal SARS-CoV-2 infection and will include fields on ultrasound diagnosis and neonatal care not included in other more general studies. This study will identify cases that should also be reported to International Network of Obstetric Survey Systems (INOSS) population-based surveillance systems of confirmed COVID-19 cases admitted to hospital through existing reporting mechanisms. The UK’s obstetric surveillance system (UKOSS) is a population surveillance study, reporting women in pregnancy hospitalised with COVID-19 or SARS-CoV-2 infection. The PAN-COVID registry is distinct in that it will collect, via a web portal, data on SARS-CoV-2 infections in pregnancy, whether the diagnosis is presumptive based on symptoms or following a positive test and whether the patient is admitted to hospital or not. Given that the SARS-CoV-2 virus is likely to affect a high proportion of the global population and adverse outcomes may influence policy and practice in a short time frame, ‘real-time’ high-level reporting on a regular basis will be valuable for UK and international clinicians and policymakers.

PAN-COVID registry will work collaboratively with approved studies and registries to ensure that the global impact of the pandemic is captured as fully as possible, with data sharing and linkage. PAN-COVID has established links with the UK National Neonatal Research Database (NNRD) (REC Reference: 16/LO/1093) who will provide data on neonatal outcomes, and the British Paediatric Surveillance Unit with whom there is in principle an agreement for data sharing. In the UK, the PAN-COVID registry will signpost to UKOSS where the case definition requires a more detailed data collection. We are in discussions with international studies including the American Academy of Pediatrics (AAP) Section of Neonatal Perinatal Medicine (SONPM) to agree on a common data set to enable future merging of information.

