### Analysis

Statistical analysis of the data will be carried out a pseudonymised data set containing NHS number (or equivalent international data field). Numerical data for cases reported and outcomes (miscarriage, SGA/FGR, stillbirth, preterm delivery and vertical transmission) will be reported in anonymised, aggregate regular reports, published on the study website.

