### Sample size

Prespecified sample size estimation was not carried out given the aim of this observational study was to collate all consecutive eligible case outcomes in participating centres between data collection start and 18 months from start of data collection. It may be useful to provide an approximate guide as to the width of the 95% CI that can be achieved for proportions using historical data from the UK. These historical data may not hold during the current pandemic and may alter due to multiple reasons such as access to healthcare or behaviour changes. Contemporaneous data collected using other current national registries will provide true background rates for comparative purposes at the end of the study period. Generalising these data internationally may not be possible unless similar contemporaneous data exist for comparison.

The estimated representative pre-COVID pandemic incidences of miscarriage, Small for Gestational Age (SGA)/FGR and stillbirth in the UK were 30%, 10%, 0.2%, respectively. The expected outcome proportions during the COVID-19 pandemic are 40%, 15% and 0.4%, respectively. A sample size of 500 would allow the estimation of the width of 95% CIs for the proportion of miscarriage as 40%±4.2%, for SGA/FGR 15%±2.9% and for stillbirth 0.4%±0.3%.

These figures are meant only as a guide and reference proportions may change over this period. Since attaining sufficient precision for stillbirth requires by far the largest sample size, then study recruitment targets could be based on this rarest of outcomes. This would then provide sufficient precision to assess other more common outcomes. These figures are based on data from the UK only. Reference proportions vary by country but are of a similar order to those in the UK.

Appropriate quantitative analyses will be conducted by a study statistician. Dates collected from sites for expected data of delivery or last menstrual period, week of pregnancy at delivery and date of any COVID-19 tests in the participant or neonate will be cross-checked and validated for the final report. Regular interim reports will use contemporaneous data as it is collated.

Derived variables to be reported are:

Infection delivery interval (<2 or≥2 weeks after onset of suspected or confirmed COVID-19).Week of pregnancy when COVID-19 diagnosis was made.Number of days from delivery to SARS-COV-2 testBirth weight percentiles adjusted for gender and gestational age.

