Fortnightly bulletins will consist of counts of participants by country, proportions for maternal COVID-19 diagnosis status (suspected, positive test, negative test), week of pregnancy for COVID-19 diagnosis (<23 weeks, 23–36 weeks, ≥37 weeks), weeks of pregnancy at delivery (<23 weeks, 23–36 weeks, ≥37 weeks), maternal and neonatal mortality, outcome of delivery (live birth, miscarriage, intrauterine death, stillbirth (>22+6 weeks gestation)), FGR split by delivery interval (<2 vs ≥2 weeks), COVID-19 diagnosis status for babies split by number of days from delivery to test (0, 1–7, 8–28) and birth weight percentiles. Mean (SD) and median birth weights will also be reported. Further analysis will take place at one interim time point and at final data collection. For the interim analysis, a subset of validated outcomes will be reported consisting of total cohort proportions of gestation at delivery, birth weight Z-scores, perinatal mortality (stillbirth, early neonatal death), neonatal COVID-19 or SARS-COV-2 swab positive, neonatal morbidity and maternal death. These data will be split by suspected and confirmed COVID-19 diagnosis. Additional graphical exploratory analysis of the data will assess any possible association between the infection delivery interval and the timing of delivery as well as birth weight. The final analysis will report all demographic baseline data for the whole cohort and all outcomes as well as these graphical trends. Proportional data for the study outcomes will be presented with 95% CIs, by country, where numbers allow. Data and all appropriate documentation will be stored for a minimum of 10 years after the completion of the study, including the follow-up period.

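### Fortnightly bulletins and the interim gestation-at-delivery proportions use immature data with no rule for ongoing pregnancies, so miscarriage figures are biased up or down depending on the denominator

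*Protocol article*

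**What the plan says.** All references are to the protocol article.

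- **Data used.** The Sample size section, which also holds the analysis text, says: "Regular interim reports will use contemporaneous data as it is collated".
- **What is published.** The Analysis section says: "Numerical data for cases reported and outcomes (miscarriage, SGA/FGR, stillbirth, preterm delivery and vertical transmission) will be reported in anonymised, aggregate regular reports". These go on the study website.
- **Bulletin content.** The fortnightly bulletins include "weeks of pregnancy at delivery (<23 weeks, 23–36 weeks, ≥37 weeks" and "outcome of delivery (live birth, miscarriage, intrauterine death, stillbirth (>22+6 weeks gestation". Both items have a value only after the pregnancy has ended.
- **Interim analysis.** At one undated time point, "a subset of validated outcomes will be reported consisting of total cohort proportions of gestation at delivery, birth weight Z-scores, perinatal mortality" and further items. Gestation at delivery is on this list; miscarriage is not.
- **Entry.** Under Study population, women are identified either at an early pregnancy attendance, with the outcome pending, or at delivery, with the outcome known.
- **End of collection.** Under Outcomes, data are collected until 28 days after the last registered woman delivers or loses the pregnancy.
- **Audience.** The Introduction says that "high-level reporting on a regular basis will be valuable for UK and international clinicians and policymakers".

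The article gives no denominator, minimum follow-up or caveat about ongoing pregnancies for the bulletins.

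**The concern.** At an early data cut, a woman infected in the first trimester can have an outcome only if she has lost the pregnancy; a woman infected at the same gestation whose pregnancy continues has none yet. Proportions among ended pregnancies therefore over-represent short pregnancies. Dividing by all registered women errs the other way, because each ongoing pregnancy is counted as free of the event.

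The reports are public, fortnightly and meant for use while the pandemic runs. The Introduction says there are no data on first-trimester miscarriage, so an early bulletin figure would have little to be checked against. The Sample size section expects miscarriage to rise from 30% to 40%, a ratio of 40/30 = 1.33. A bias larger than that could be read as confirming the expected rise, or could hide it. A sound final report cannot undo decisions taken on earlier bulletins.

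**Working it through.** The article states no figure for interim bias, so there is none to reproduce. Its Introduction does show that unresolved pregnancies are common: in the UK study it cites, 247 of 427 cases were completed pregnancies, leaving (427 − 247)/427 = 42% unresolved.

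**Inputs from the article.** Infections from January 2020 to March 2021 (about 62 weeks); loss risk 30% historically and 40% expected.

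**Assumptions not in the article.** Steady conceptions; infection possible from 5 weeks' gestation; losses mostly at 7 to 14 weeks; 8% of births preterm; registration at infection; infection constant over time; no effect of infection on outcome.

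**Quantities at a cut t weeks after the start.**

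- Completed denominator: C(t) = losses by t / (losses + births by t).
- All-registered denominator: A(t) = losses by t / women registered by t.
- Reference: the same cohort fully followed.

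It follows that A(t)/C(t) is the share of registered women whose pregnancy has ended.

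**Miscarriage, 30% loss risk, reference 5.9%**

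| Cut (weeks) | C(t) | C/5.9 | A(t) | A/5.9 | Ended share A/C |
|---|---|---|---|---|---|
| 4 | 29.5% | 5.0 | 2.3% | 0.39 | 0.08 |
| 12 | 21.3% | 3.6 | 4.5% | 0.76 | 0.21 |
| 26 | 12.8% | 2.2 | 5.2% | 0.88 | 0.41 |
| 52 | 8.1% | 1.4 | 5.6% | 0.95 | 0.69 |

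The reference is 5.9% and not 30% because most women are infected after the weeks in which losses occur.

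**Sensitivity at 12 weeks.** With 40% loss risk, C = 29.7% against 8.9%, a ratio of 3.3. With 30% loss risk and all infections in an 8-week wave, C = 20.0% against 5.9%, a ratio of 3.4. A separate simulation at 13 weeks gave 20% among completed and 4.4% among all registered, against 6.0%; 20/6.0 = 3.3.

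**Preterm birth, pooled over all infected women.** Among completed births: 7.6%, 8.0%, 7.9% and 7.2% at the four cuts, against 6.8%; the largest ratio is 8.0/6.8 = 1.18. Among all registered women: 0.4%, 1.3%, 2.8% and 4.5%, against 6.4%.

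**Candidate remedies.**

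- *Restrict to women whose due date plus 28 days has passed, pooled.* Maturity is then reached at 44 weeks' gestation. At a 13-week cut only women infected at 44 − 13 = 31 weeks or later can qualify; at 26 weeks, only those infected at 44 − 26 = 18 weeks or later. Nearly all are past the weeks in which most losses occur, and simulated miscarriage was 0% at both cuts.
- *Cumulative incidence by gestational week with delayed entry.* F(g) = Σ S(gⱼ−)·dⱼ/nⱼ, where dⱼ is the number of losses at gestation gⱼ, nⱼ is the number of women already entered and still under observation, and S is the probability of still being pregnant. It gave 28–30% against the true 30% at every cut. It estimates loss risk from early pregnancy, the scale of the article's 30% background rate.

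**The case against.** **The sentence is about validation.** The sentence before it promises date checks for the final report, so the contrast may be checked against unchecked data. That is a fair reading. It is still the only statement of which data enter the regular reports, and it sets no maturity condition.

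**Denominators can be left to the full protocol or analysis plan.** This is true of a table footnote. Here, though, neither obvious denominator gives a correct figure, so choosing between them does not solve the problem. The article itself fixes the fortnightly reporting of delivery outcomes from data as they accrue.

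**Direction.** A reader might infer that early figures are certain to be badly inflated. The documents do not support that: inflation needs a completed-pregnancy denominator, which the article does not state, and the interim wording about the total cohort could mean all registered women, which lowers the figures.

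**Extreme strata.** Among women infected before 13 weeks, the simulation gives 97.5% miscarriage of completed pregnancies at 26 weeks, against 20.8% fully followed. The article does not plan to tabulate outcome by gestation at infection, so this figure shows the mechanism, not a planned table.

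**Women identified at delivery have no pending outcome.** That is correct, but comparable women who are still pregnant are not yet registered, so this group is itself selected at an early cut.

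**Interim and final analyses.** The interim analysis is undated and does not list miscarriage, so no size can be put on its bias. The final analysis is complete under the article's end-of-collection rule. Both points stand.

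**Conclusion.** The point holds for the bulletins and for the interim gestation-at-delivery proportions. As planned, they summarise a cohort with many ongoing pregnancies, and simple proportions mislead on either denominator. On the stated assumptions, miscarriage at about three months is inflated some 3.3- to 3.6-fold among completed pregnancies, and is about a quarter too low among all registered women (4.5% against 5.9%). Pooled preterm birth is inflated by at most about 1.2-fold among completed births, and is understated among all registered women.

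The mechanism does not depend on the simulation. The sizes do: they rest on assumed timing of losses, pattern of infection and registration at infection, and are illustrative. The point does not extend to the final analysis, and it does not show that published figures would necessarily be too high.

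**What to change.** In the bulletins and the interim analysis:

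1. Report pregnancy loss and preterm birth as Aalen-Johansen cumulative incidence by gestational week, with delayed entry at the later of infection and registration, and with ongoing pregnancies censored at the data cut.
2. Report women first registered at delivery or loss in a separate table. They contribute no observed time at risk and are selected on the pregnancy having ended.
3. Print the number still pregnant beside each outcome table.
4. Use a due-date-passed restriction only within strata of gestation at infection. Pooled, it holds almost only late-pregnancy infections and drives miscarriage towards zero.

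The Data entry section already lists last menstrual period, due date, test dates and date of delivery or miscarriage; the registration date is also needed for the entry time. The cost is some programming and wide intervals in early bulletins. The bulletins should also say that the cumulative incidence is a risk over gestation, so that it is not compared with a crude proportion of registered women.

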### Data entry

Demographics—date of birth, National Health Service (NHS) number (or international equivalent), smoking status, last menstrual period, expected date of delivery, body mass index, history of previous pregnancies/miscarriages/loss/small for gestational age/delivery (preterm/term), comorbidities, medications, ethnicity, number of fetuses, structural abnormality on ultrasound.

COVID-19 signs and symptoms—fever, new persistent cough, anosmia, myalgia, diarrhoea, shortness of breath, fatigue, abdominal pain, chest pain, hoarseness of voice, loss of appetite, delirium.

SARS-CoV-2 infection—SARS-CoV 2 test performed, date of test(s), results of test(s) (if available)

COVID-19 treatment—requirement for (including duration of) inpatient, level 2 or 3 critical care, supplementary oxygen, non-invasive ventilation, endotracheal intubation, extracorporeal membrane oxygenation, antiviral/other specific anti-COVID-19 therapy, iatrogenic delivery or termination due to maternal compromised from COVID-19.

Maternal outcomes—non-invasive ventilation, intubation and ventilation and maternal death.

Comorbidities—hypertension, respiratory disease, cardiovascular disease, renal disease, autoimmune disease, medications including aspirin, progesterone, others.

Delivery details—iatrogenic/spontaneous, date of delivery/miscarriage, mode of delivery, live birth/stillbirth/miscarriage, birth weight, sex.

Postnatal outcomes—breastfeeding, baby cared for separately from mother until discharge.

Neonatal outcomes—date of birth, birth weight, gestation at birth, Apgar at 5 min, neonatal death, COVID-19 transmission (neonate with positive swab/serology), congenital abnormality/deformation, date of discharge from hospital, readmission up to 28 days of life.

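### The exploratory graph of infection-delivery interval against timing of delivery has a positive association built into it, as does the birth-weight graph if raw weight is plotted

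*Protocol article*

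**What the plan says.** The Sample size section lists among its derived variables the "Infection delivery interval (<2 or≥2 weeks after onset of suspected or confirmed COVID-19". The analysis text that follows uses the interval twice. The fortnightly bulletins split FGR at under 2 versus 2 or more weeks. The interim and final analyses add graphs to "assess any possible association between the infection delivery interval and the timing of delivery as well as birth weight". The graphs are described as exploratory, with no test or model, and the final report is to include the trends. Nothing is said about conditioning on gestation at infection.

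The same section derives birth weight percentiles adjusted for sex and gestational age, and the interim report gives birth weight Z-scores. The text does not say which scale the birth-weight graph uses.

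On dates, the Data entry section lists symptoms ("fever, new persistent cough, anosmia, myalgia, diarrhoea, shortness of breath, fatigue" and others) without an onset date. For infection it lists "SARS-CoV 2 test performed, date of test(s), results of test(s) (if available". The Sample size section says that the expected delivery date or last menstrual period, "week of pregnancy at delivery and date of any COVID-19 tests in the participant or neonate will be cross-checked" and validated. The Introduction makes clear that women are registered "whether the diagnosis is presumptive based on symptoms or following a positive test", so some have no test.

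**The concern.** Gestation at delivery, gestation at infection and the interval are tied by an identity: the first is the sum of the other two. A graph of delivery timing against the interval therefore slopes upward even if infection does nothing. Raw birth weight rises with gestation, so it picks up the same slope.

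A reader would naturally take such a graph to mean that infection precipitates early delivery, or that babies born soon after infection are lighter. The Introduction expects the registry's outputs to influence policy and practice quickly, so a pattern produced by the construction of the plot is worth avoiding even in an exploratory figure.

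**Working it through.** The article gives no figure for the interval, so there is none to reproduce. The check is the identity, followed by a simulation in which infection has no effect.

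**1. Identity.** Let T be gestation at infection, D gestation at delivery and I the interval. Then D = T + I. Using the article's own gestation bands:
- Infection before 23 weeks with I < 2 forces delivery before 23 + 2 = 25 weeks.
- Infection at 37 weeks or later can never end in preterm delivery.

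**2. Size of the built-in correlation.** Suppose infection is spread evenly from week *a* and must only precede delivery. Then the mean of I given D is (D − a)/2, so Cov(I, D) = Var(D)/2 and

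corr(I, D) = 0.5 × SD(D) / SD(I).

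This is positive whenever D varies.

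**3. Numbers.** There were 2 million simulated pregnancies per run, keeping those infected before delivery. Assumptions:
- Term births centre on 39.6 weeks (SD 1.2, held to 37–42).
- Preterm births fall at 24–37 weeks, skewed towards 37.
- The preterm proportion is 8% (assumed) or 94/428 = 22% (the review of published cases cited in the Introduction).
- Infection is uniform from week 4 or from week 28, up to week 42.

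| Infections from | Preterm | SD(D), weeks | SD(I), weeks | 0.5 × SD(D)/SD(I) | Simulated correlation |
|---|---|---|---|---|---|
| week 4 | 8% | 1.92 | 10.24 | 0.09 | 0.09 |
| week 4 | 22% | 2.67 | 10.09 | 0.13 | 0.13 |
| week 28 | 8% | 1.54 | 3.44 | 0.22 | 0.22 |
| week 28 | 22% | 2.03 | 3.42 | 0.30 | 0.30 |

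Formula and simulation agree. If 30% of cases are first detected at admission for delivery (infections from week 4, 8% preterm), the correlation is 0.08. A separate null simulation gave 0.08–0.12 for the whole cohort and 0.20–0.27 for infections from week 28.

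The same runs, expressed as preterm birth for intervals under 2 versus 2 or more weeks, give 8.0% vs 6.7% and 21.9% vs 18.9% for the whole cohort. From week 28 they give 7.6% vs 3.4% and 20.9% vs 10.3%.

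**4. Birth weight.** Mean weight was made to depend on gestation only. Raw weight was then about 27–59 g lower with an interval under 2 weeks over the whole cohort, and about 89 g or 182 g lower with infections from week 28. Mean Z-score differed by 0.003 or less in every run. The artefact belongs to the raw scale.

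**5. FGR split.** If FGR does not depend on gestation at delivery, the split shows nothing (15.0% vs 15.0%). If FGR is assumed to be 30% in preterm and 10% in term births:
- Whole cohort: 11.7% vs 11.4%, or 14.4% vs 13.8%.
- Infections from week 28: 11.5% vs 10.7%, or 14.2% vs 12.1%.
- Within infection at 23–36 weeks: 19% vs 11%, or 24% vs 13%.

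Splitting by interval inside gestation bands enlarges the artefact.

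**6. Does the replacement remove it?** In the null runs with infections from week 4, take women still pregnant at 34 weeks and count delivery before 37 weeks, by gestation at onset (before 23, 23 to under 30, 30 to under 34). The result is 4.5% in all three bands with 8% preterm, and 13.1–13.3% with 22% preterm. Counting forward from a common gestation, without using the realised interval, gives flat results when there is no effect.

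**The case against.** The strongest reply is that these are exploratory graphs with no test, model or causal claim, in a registry whose research question is incidence. Over the whole cohort the built-in correlation is only about 0.1. That stands, and it limits the consequence to interpretation. It does not justify plotting a sum against its own part when a clean display uses the same data.

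Three stronger readings are tempting, and the documents do not support them.

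- *Onset is not collected, so the interval cannot be derived for untested women.* The Data entry list is condensed. Its neonatal line gives transmission by swab or serology with no date, yet the Sample size section says that "date of any COVID-19 tests in the participant or neonate will be cross-checked and validated for the final report". Absence from that list is therefore not evidence of absence from the database. Nor does the article say that a test date replaces onset. What remains is that the anchor is unexplained.
- *The FGR split in the bulletins is seriously distorted.* It needs FGR to vary with gestation at delivery. Even with a threefold risk in preterm births, the gap is about 0.3–0.6 points overall and about 2 points at most if infections start at week 28.
- *Preterm birth will look several times more frequent after a short interval.* Within infection at 23–36 weeks the null simulation does give about 43% vs 5%, or 71% vs 15%. The plan, however, contains no table of preterm birth by interval within diagnosis bands. Week at diagnosis is a separate summary.

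On birth weight, the plan already derives gestation-adjusted percentiles and Z-scores, so the problem arises only if raw weight is plotted. The article leaves that open.

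**Conclusion.** The point holds for the graphs. The delivery-timing graph will show a positive association with no effect of infection, and so will the birth-weight graph if it uses raw weight. The direction follows from the identity and from infection having to precede delivery. The size rests on the assumed distributions: a null correlation of about 0.08–0.13 for the whole cohort and about 0.20–0.30 if mostly late infections are registered. The mix of gestations actually registered decides where the study falls.

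The incidence estimates are unaffected. The unstated anchor date is a minor point of clarity and not a demonstrated gap in data collection.

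**What to change.** 1. Replace the graph of interval against delivery timing with time from onset to delivery, shown as delayed-entry cumulative incidence by gestational age, given gestation at onset. Do not group on the realised interval.
2. State that the birth-weight graph uses the Z-scores or percentiles already planned, not raw weight.
3. Show FGR by gestation at onset. Do not split it by interval within gestation bands, since that makes the artefact larger.
4. State which date serves as onset for tested women and for untested suspected women.

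The cost is slightly more analysis work. Some onset dates will be approximate, and the report should say so.

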As of the 12 May 2020, after disambiguation and removal of duplicate reporting, the rolling review of all cases worldwide conducted by Thornton et al^10^ contains 92 publications including details of 806 pregnant women and 674 fetuses. At the time of writing this protocol, 457 of the included women had delivered and were alive and 21 women had died. These women had delivered 428 babies, of which 94 were born preterm, 17 were infected with COVID-19, and there were 15 neonatal deaths. The largest study to date has been from the UK (Knight et al) who reported 427 cases (247 completed pregnancies): there were five (1%) maternal deaths, three (1%) stillbirths and two (1%) neonatal deaths.^11^ There are currently limited data on the effect of COVID-19 on second trimester miscarriage^12^ and no available data on first trimester miscarriage or growth restriction. The risk of reported probable vertical transmission of SARS-CoV-2 infection is estimated at 2.5% in women admitted to hospital with COVID-19; with case reports describing increased SARS-CoV-2 IgM levels in neonates, and pneumonia and lymphopaenia in neonates with negative COVID-19 reverse transcription-PCR testing, principally from nasopharyngeal swabs.^13 14^

There are major knowledge gaps on the effect of COVID-19 on various stages of pregnancy, and its effect on fetuses in terms of growth restriction, prematurity and short and long term morbidities.^15^ There is an urgent need to collect case data rapidly, to pool global data on the natural history of women affected by suspected COVID-19 or confirmed SARS-CoV-2 in pregnancy to inform treatment and implement preventative strategies in the current and future outbreaks. Published case series are almost always out of date when published and cases may overlap. A centre-based registry, gathering case data prospectively on the effect of SARS-CoV-2 infection from healthcare systems around the world offers a method to accrue clinical outcomes on key research questions from a variety of populations and healthcare systems without these limitations.

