## Methods and analysis

This is an observational global pregnancy and neonatal register (PAN-COVID registry) collecting outcome data from women in pregnancy who have confirmed SARS-CoV-2 infection or signs and symptoms of COVID-19 during their pregnancy. The study is sponsored by Imperial College London and funded by UK Research Institute and National Institute of Health and Research (NIHR). The study received Urgent Public Health (UPH) prioritisation in the UK in April 2020.

The main study objectives are, first, to establish a UK and international disease registry for women with suspected COVID-19 or confirmed SARS-CoV-2 infection in pregnancy; in the UK, this will be linked to neonatal data (from NNRD). Second, PAN-COVID investigators aim to publish regular reports focused on our principle research question: in women recruited to the PAN-COVID registry with suspected or confirmed SARS-CoV-2 infection, what is the incidence of (a) miscarriage, (b) small for gestational age (SGA)/FGR and stillbirth, (c) preterm birth and (d) suspected or confirmed vertical transmission to the neonate and perinatal infection.

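### The bulletins' single band below 23 weeks merges first- and second-trimester infection and loss, and no stated miscarriage proportion is protected from shifts in gestation mix

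*Protocol article*

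**What the plan says.** The gestation bands appear in the analysis text at the end of the Sample size section of the protocol article, in the sentence that opens "Fortnightly bulletins will consist of counts of participants by country". That sentence bands "week of pregnancy for COVID-19 diagnosis (<23 weeks, 23–36 weeks, ≥37 weeks" and repeats the cuts for "weeks of pregnancy at delivery (<23 weeks, 23–36 weeks, ≥37 weeks". It lists the result of the pregnancy as "outcome of delivery (live birth, miscarriage, intrauterine death, stillbirth (>22+6 weeks gestation", so miscarriage is one category with no trimester attached.

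The same text says that outcome proportions will carry 95% CIs by country where numbers allow. No other stratifier is named for those proportions. The interim analysis lists its own subset of outcomes, and miscarriage is not among them. The final analysis covers all outcomes and states no gestation bands.

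The Introduction says there are "no available data on first trimester miscarriage or growth restriction", treats second-trimester miscarriage separately as an area with limited data, and adds: "There are major knowledge gaps on the effect of COVID-19 on various stages of pregnancy". The research question in Methods and analysis asks "what is the incidence of (a) miscarriage, (b) small for gestational age (SGA)/FGR and stillbirth, (c) preterm birth", with no trimester named.

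Finer information is held. The derived variables include "Week of pregnancy when COVID-19 diagnosis was made", and the Data entry section collects last menstrual period, expected date of delivery and date of miscarriage.

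**The concern.** The cut at 23 weeks suits the stillbirth and preterm questions. For miscarriage it gives no resolution: with stillbirth starting after 22+6 weeks, every miscarriage falls in the lowest band. The Introduction distinguishes first- from second-trimester loss, and the bulletin layout merges the two.

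The second problem is comparability. Under Study population, women are identified at an early pregnancy attendance or at delivery. Centres that contribute mainly from one route will supply different gestations from centres that use the other. If loss risk differs by gestation at infection, a proportion taken over all registrations can differ between bulletins or countries with no change in risk at any gestation. Reporting by country does not remove this, because countries can differ in recruitment route. A woman diagnosed at 23 weeks or later adds to a whole-cohort denominator but can no longer miscarry under the plan's own cut-off.

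**Working it through.** **The plan's own miscarriage figure.** The Sample size section gives 40% ± 4.2 points at 500 women. The normal approximation gives 1.96 × √(0.40 × 0.60 / 500) = 4.29 points, so the stated width is not quite reproduced. That is a separate matter, and nothing below depends on it.

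**Inputs.** The article gives an overall pre-pandemic UK miscarriage incidence of 30% and an expected 40% during the pandemic. It gives no trimester-specific risks and no gestation distribution of registrations. The following are therefore assumptions, shown over a range:

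- r1: miscarriage risk after first-trimester infection
- r2: miscarriage risk after infection from 14 to 22+6 weeks
- w: first-trimester share of women diagnosed before 23 weeks
- f: share of the whole cohort diagnosed before 23 weeks

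**Step 1: women diagnosed before 23 weeks.** Pooled proportion P = w × r1 + (1 − w) × r2. For example, with r1 = 30% and r2 = 1%: 0.2 × 30 + 0.8 × 1 = 6.8%, and 0.8 × 30 + 0.2 × 1 = 24.2%.

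| r1 | r2 | w = 20% | w = 50% | w = 80% | Change, 20% to 80% |
|---|---|---|---|---|---|
| 10% | 5% | 6.0% | 7.5% | 9.0% | 3.0 points |
| 20% | 2% | 5.6% | 11.0% | 16.4% | 10.8 points |
| 30% | 1% | 6.8% | 15.5% | 24.2% | 17.4 points |
| 30% | 3% | 8.4% | 16.5% | 24.6% | 16.2 points |
| 40% | 2% | 9.6% | 21.0% | 32.4% | 22.8 points |

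The change is 0.6 × (r1 − r2). It is non-zero whenever the two risks differ, and its size is set entirely by the assumed gap.

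**Step 2: the whole cohort.** Women diagnosed at 23 weeks or later contribute no miscarriages, so the whole-cohort proportion is f × P. With r1 = 30%, r2 = 2% and w = 50%, P = 0.5 × 30 + 0.5 × 2 = 16.0%. The whole-cohort figure is then 0.5 × 16.0 = 8.0% if half the cohort was diagnosed before 23 weeks, and 0.3 × 16.0 = 4.8% if 30% was. This is a second route by which mix alone moves the figure.

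**Step 3: precision on the at-risk denominator.** At 40% and 500 registrations, the half-width is 6.1 points if 250 women were diagnosed before 23 weeks, 7.8 points if 150 were, and 13.6 points if 50 were. Splitting that group at 14 weeks widens the intervals further.

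**The case against.** The strongest reply is about scope. The bands stand in the sentence on bulletins, which are rapid summaries. The final analysis is described separately and is not tied to them, and week of diagnosis is a derived variable without bands. A reader might infer that the registry cannot answer the first-trimester question at all. The article does not support that: the dates are collected, and an analysis plan that is not shown may define finer groups.

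A reader might also infer that the plan will publish a miscarriage rate among women diagnosed before 23 weeks. It does not say so. Diagnosis week, delivery week and outcome are listed as separate items, and no denominator for miscarriage is stated. Step 1 is therefore an illustration and does not criticise a planned statistic.

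A third tempting reading is that the artefact exceeds the 10-point rise from 30% to 40% that the plan expects. That holds for some assumed rates and fails for others: the 10%/5% case moves only 3 points. The 30% is the plan's overall incidence, not a risk after first-trimester infection, and nothing in the article shows that the mix would shift from 20% to 80%.

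The first-trimester gap is background to the study and not a separate objective, so there is no formal contradiction. The 23-week cut also has a purpose, since it matches the stillbirth threshold and gives larger cells.

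What remains is narrower. The bulletins are the only itemised output that names miscarriage before the final report, and the Introduction values real-time reporting because outcomes may influence policy quickly. In the outputs as stated, first-trimester loss is not visible, and nothing guards a miscarriage proportion against changes in mix.

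**Conclusion.** The point holds as a modest, low-cost improvement to reporting. The bulletin bands place first- and second-trimester infection and loss in one cell, and country is the only stratifier stated for proportions with confidence intervals, although the Introduction names the first-trimester gap and miscarriage is part (a) of the research question.

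That a whole-cohort miscarriage proportion depends on gestation mix follows from two things: the plan's stillbirth threshold, and any difference in risk between early and later infection. The direction was the same for every pair of assumed rates. The size cannot be fixed from the article; a fair statement is from about 3 points (10%/5%) to about 16–17 points (30%/1–3%) as the first-trimester share goes from 20% to 80%, and larger if the risk gap is wider. The point does not extend to the interim analysis, and it does not show that the final analysis will be wrong.

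**What to change.** In the bulletins and the final report, split the band below 23 weeks into <14 weeks and 14 to 22+6 weeks, for both week of diagnosis and week of loss. Report the miscarriage proportion with a 95% CI within each infection band, taking only women diagnosed before 23 weeks as the denominator. The interim analysis needs no change.

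No new data are needed, because last menstrual period, expected date of delivery, date of miscarriage and week of diagnosis are already collected or derived. The cost is smaller cells and wider intervals in early bulletins. The split also leaves some variation in risk within each band: women at 6 and 13 weeks would still share one, so gestation mix and time of entry would keep some influence.
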